## Abstract

**Background:**

Continuous renal replacement therapy (CRRT) is the recommended modality of dialysis for critically ill patients with hemodynamic instability. Yet there remains significant variability in how CRRT is prescribed and delivered, and limited evidence-basis to guide practice.

**Methods:**

This is a prospective, multi-center observational study of patients undergoing CRRT. Initial enrollment phase will occur at 4 academic medical centers in North America over 5 years, with a target enrollment of 2000 patients. All adult patients (18–89 years of age) receiving CRRT will be eligible for inclusion; patients who undergo CRRT for less than 24 h will be excluded from analysis. Data collection will include patient characteristics at baseline and at time of CRRT initiation; details of CRRT prescription and delivery, including machine-generated treatment data; and patient outcomes.

**Discussion:**

The goal of this study is to establish a large comprehensive registry of critically ill adults receiving CRRT. Specific aims include describing variations in CRRT prescription and delivery across quality domains; validating quality measures for CRRT care by correlating processes and outcomes; and establishing a large registry for use in quality improvement and benchmarking efforts. For initial analyses, some particular areas of interest are anticoagulation protocols; approach to fluid overload; CRRT-related workload; and patient safety.

**Trial registration:**

Registered on ClinicalTrials.gov 1/10/2014: NCT02034448.

## Background

Acute kidney injury (AKI) occurs commonly in critically ill patients, complicating more than half of intensive care unit (ICU) admissions [1, 2]. About 5–6% of ICU patients will receive renal replacement therapy (RRT), and hospital mortality rates in this population approach or exceed 50% [3–6]. Despite the major clinical significance of this syndrome, there remains no proven therapy to reverse or attenuate established AKI, and care is primarily supportive, including RRT in severe cases.

For ICU patients, particularly those with hemodynamic instability, continuous renal replacement therapy (CRRT) has emerged as the dialysis modality of choice in high-income nations. Since the original descriptions of continuous arteriovenous hemofiltration over 30 years ago, [7] CRRT has undergone significant evolution with several improvements allowing more widespread and routine use. Advancements include peristaltic pump driven venovenous circulation, sophisticated hardware and software engineering for precise application of the prescribed treatment and enhanced safety and alarms, improved biocompatibility and other membrane characteristics, regional anticoagulation protocols and enhancements in user interface. Indeed, for hemodynamically unstable patients the 2012 Kidney Disease: Improving Global Outcomes (KDIGO) AKI guidelines suggest using CRRT over intermittent dialysis options [8]. Compared to standard intermittent hemodialysis (IHD), CRRT offers advantages of improved hemodynamic stability, better overall solute clearance, and better fluid balance [8–10]. Observational studies also suggest higher rates of renal recovery among patients initially treated with CRRT compared to conventional IHD, although this benefit has not been observed in randomized trials [11].

While the clinical role of CRRT has become well-established, there exists tremendous variability in how CRRT is prescribed and delivered [12–14]. The KDIGO AKI guidelines provide some recommendations, stating that the target delivered CRRT effluent dose should be 20–25 mL/kg/h, and also suggesting that regional citrate should be the first-line form of anticoagulation [8]. However, specific recommendations are lacking for a number of other important areas, such as CRRT modality, details of anticoagulation protocols, electrolyte supplementation practices, or approach to fluid balance. This reflects the lack of strong evidence upon which to base guidelines, as most studies examining CRRT practices have been relatively small and/or single-center. In addition, despite the high-risk nature of the patient population, very few studies have examined quality metrics and/or patient safety related to CRRT practices [15].

Here we describe the protocol for a prospective observational study focused on CRRT practices in critically ill adult patients across a network of medical centers in North America (CRRTnet). Our goal is to develop a large repository of data regarding CRRT practices and outcomes, allowing characterization of similarities and differences in standard CRRT practices across medical centers. The natural variability in practices between (and even within) centers will provide the ability to compare outcomes between different practice patterns and generate important preliminary data to inform future interventional trials. In addition, a long-term goal for CRRTnet is to establish benchmarks for best CRRT practice for centers both within and outside the study.

## Methods/design

### Study oversight and consent

This study was registered on ClinicalTrials.gov before initiation of recruitment (identifier NCT02034448). Each of the initial recruitment centers has received local institutional review board approval for CRRTnet with a waiver for informed consent. This waiver was granted due to the minimal risk nature of this observational study, as well as the recognition that this study would not be practical without the waiver. Specifically, since no interventions are involved, patient recruitment into the database may occur on a retrospective basis and it would be inefficient and possibly emotionally distressing to contact patients or their families for consent after the fact. Furthermore, it is important to include all CRRT patients in order to provide an unbiased perspective of practice patterns and maximize validity of our findings.

Ongoing study oversight will be performed by the CRRTnet registry board, which is chaired by [name] and comprised of the site principal investigators for each of the recruitment centers.

### Design and setting

This is a prospective, multi-center observational study of critically ill adults undergoing CRRT. Initial recruitment is planned at 4 academic medical centers in North America with significant (>50 patients per year) volume CRRT use: University of Michigan Health System (Ann Arbor, MI), University of Alberta Hospital, University of Alberta (Edmonton, Alberta), University Hospital London Health Sciences Centre (London, Ontario), and University of Mississippi Medical Center (Jackson, MS).

### Patient population

All subjects in this study will be critically ill adult patients with AKI receiving CRRT as part of their standard of care. Inclusion criteria are age ≥ 18 years and ≤89 years. Exclusion criteria are patients who receive CRRT for less than 24 h, and those who are initiated on CRRT at an outside hospital prior to transfer in whom incomplete data are available. For patients who require multiple courses of CRRT during an admission, only the data from the first course will be considered. Patients with pre-existing end-stage renal disease on maintenance dialysis are also excluded.

### Data collection

Data will be collected encompassing a wide range of variables examining patient characteristics at enrollment, describing daily ICU course, capturing details of CRRT, and describing patient outcomes. Each participating medical center utilizes an electronic medical record which will serve as the primary source for data extraction.

The initial intake form includes demographic variables, and baseline patient characteristics at the time of CRRT initiation (Table 1). Fluid balance (in liters) between the time of ICU admission and CRRT initiation will be collected and used to calculate percent fluid overload using the following formula: [16, 17].

**Table 1 Tab1:** Planned data collection at time of enrollment (CRRT initiation)

Category	Data Elements
Demographics	Date of birth/Age
	Gender
	Body mass index
	Hospital admission weight
Comorbidities	Components of Charlson Index
ICU Admission Data	ICU admission date
	Admission source (hospital ward, emergency department, outside hospital transfer)
	Primary condition
	Secondary condition
CRRT Initiation Data	Clinical indication for CRRT (all that apply)
	Time from ICU admission to CRRT initiation
	Cumulative fluid balance from ICU initiation to CRRT initiation
Laboratory Data	Serum creatinine at ICU admission
	Serum creatinine at CRRT initiation
	APACHE II score at ICU admission

*CRRT* continuous renal replacement theray, *ICU* intensive care unit

%fluid overload = [(total fluid intake (L) – total fluid output (L))/ICU admission weight (kg)] x 100%. Additional patient clinical data will be updated on a daily basis to reflect clinical management, severity of illness and laboratory findings (Table 2). All laboratory values will be recorded as available, and no laboratory testing will be requested as part of CRRTnet.

**Table 2 Tab2:** Daily clinical data collection

Category	Data Elements
Severity of Illness	SOFA score components
	Need for mechanical ventilation
	Vasopressor requirements (drug and rate)
Fluid Balance	Type and volume of fluid intake
	Type and volume of recorded outputs
Nutrition	Enteral nutrition formula and volume
	Parenteral nutrition protein, calories and volume
Laboratory Data	Complete blood count: white blood cell count, hemoglobin, hematocrit, platelets
	Metabolic panel: sodium, potassium, chloride, bicarbonate, blood urea nitrogen, creatinine, phosphate, magnesium, albumin
	Coagulation parameters: INR, PTT, anti-Xa activity
	Blood gas: pH, PaO2, PaCO2, lactate, ionized calcium

For up to the first 7 days of a patient’s CRRT course, data regarding CRRT prescription and delivery will be recorded twice daily (Table 3). For days 8 thru 14, CRRT data will be captured once daily. Details of the CRRT prescription will be truncated at 14 days. Each of the initial recruitment centers performs CRRT utilizing the Prismaflex™ device (Baxter International Inc.) which has a datacard to which machine treatment data are automatically saved. These data include detailed information such as pressure measurements, fluid removal, delivered CRRT effluent dose, and all alarms, interruptions and interventions. Machine treatment data files will be downloaded and analyzed for each patient. Each site will de-identify the patient file using the de-identified patient ID assigned by the registry database in place of the patient identifier. The de-identified machine data files will be uploaded by the site into the CRRTnet Registry within each patient’s record. Data is parsed by the application and stored in the database into select data fields based on dates and time points for each day the patient is on CRRT. If the data files cannot be accessed/used, the site can manually fill in the data fields for the specified time points with data collected by the medical staff.

**Table 3 Tab3:** Daily CRRT data collection

Category	Data Elements
Vascular Access	Dialysis catheter position
	Dialysis catheter type (acute or tunneled)
	Dialysis catheter manufacturer
	Dialysis catheter size
	Any need for catheter manipulation (e.g. repositioning, replacement)
CRRT Circuit	Any circuit interruptions/replacements and reasons
	Priming solution (new circuits)
CRRT-Related Anticoagulation	Anticoagulation type (heparin, citrate, none, other)
	Anticoagulation dose
	Anticoagulation metrics
CRRT Fluids	Type of solution
	Modality (dialysate, pre- and/or post-replacement) and rate
	Solution additives
CRRT Dose	Prescribed effluent dose
Machine Data Card	Delivered effluent dose
	Type, number and duration of machine alarms and interruptions
	Filter life

*CRRT* continuous renal replacement theray

Data entry will be performed by trained study staff at each site, and will be entered into an online system using a password-protected web-based research interface (Watermark EDGE, Watermark Research Partners, Inc.). Electronic data transmission will utilize secure socket layer (SSL) encryption technology to maintain compliance with privacy and data security. Data within the Watermark EDGE database is protected by Transparent Data Encryption (TDE) encrypted with the AES-265 Cipher. Limited Data Set (LDS) will be collected with regards to specific dates for the following: year of birth, admission dates, treatment dates, date of discharge or death. For patient data entry each patient will be de-identified via assigned unique codes and will not contain direct traceable identifiers. This registry complies with the following as set forth in 45 CFR Parts 160 and 164 (“HIPAA Privacy Rule”): “Covered Entity” (45 CFR § 160.103), “De-identified information” (45 CFR § 164.514), “Protected Health Information (“PHI”)” (45 CFR § 164.103) and “Limited Data Set (“LDS”)” (45 CFR 164.514(e)(2)). All sites will utilize the same electronic report forms, with the exception of measurement units customized to match each center’s customary laboratory reporting. For purposes of analysis all unit values entered by the center will also be converted and stored in a standardized unit for reporting in addition to the original entry.

### Interventions

CRRTnet is strictly an observational study and no clinical interventions will be performed. In addition, no biosample collection or storage will occur as part of CRRTnet.

### Operational definitions

Complete recovery: - Return of serum creatinine (SCr) to within 50% of baseline. Baseline SCr will be determined by the order of the following:
i.pre-hospital/outpatient SCr valuesii.lowest available in-hospital SCr (before or after) receiving CRRTiii.back calculation for a SCr based on an eGFR 75 mL/min using the CKD-EPI equation
2.Partial recovery: - No longer receiving RRT but SCr has not returned to within 50% of baseline.3.Non-recovery: - Remains dialysis dependent.

All serious adverse events related to CRRT will be recorded, with a specific focus on the following complications:Major bleeding event related to heparin anticoagulation:
i.Drop in hemoglobin of ≥1.0 g/dL within a 24 h period, *and*
ii.Transfusion requirement of ≥2 units packed red blood cells
2.Development of heparin-induced thrombocytopenia:
i.Fall in platelets of at least 30% *and*
ii.Positive confirmatory test for heparin-induced thrombocytopenia (serotonin release assay)
3.Hypocalcemia event related to citrate anticoagulation:
i.Fall in systemic ionized calcium below 0.8 mmol/L, *and one of the following*
ii.Worsening hypotension/increasing pressor requirement, *or*
iii.Cardiac arrhythmia

All serious adverse events will be reviewed with each site’s principal investigator to confirm appropriateness for inclusion.

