### Primary and secondary outcomes

The primary outcome will be patient survival at ICU discharge. Patient outcomes will also be recorded at hospital discharge. Additional outcomes include ICU and hospital length of stay, renal function recovery during hospitalization (defined above), and adverse events related to CRRT (defined above).

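### Major bleeding is defined only for heparin and symptomatic hypocalcemia only for citrate, so these two endpoints, as worded, cannot be compared between anticoagulation strategies

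*Protocol article*

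**What the plan says.** Operational definitions sets the scope of safety recording: "All serious adverse events related to CRRT will be recorded, with a specific focus on the following complications". Three complications follow.

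- "Major bleeding event related to heparin anticoagulation": a hemoglobin fall of at least 1.0 g/dL within 24 hours, together with at least 2 units of red cells.
- "Development of heparin-induced thrombocytopenia": a platelet fall of at least 30% with a positive confirmatory test.
- "Hypocalcemia event related to citrate anticoagulation": systemic ionized calcium below 0.8 mmol/L, with either worsening hypotension or pressor need, or an arrhythmia.

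The section then adds a review step: "All serious adverse events will be reviewed with each site’s principal investigator to confirm appropriateness for inclusion". Primary and secondary outcomes lists "adverse events related to CRRT (defined above") among the additional outcomes. In the abstract, the topics for initial analyses are given as follows: "some particular areas of interest are anticoagulation protocols; approach to fluid overload; CRRT-related workload; and patient safety". Table 3 records the anticoagulant as heparin, citrate, none or other.

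**The concern.** The criteria under the bleeding and hypocalcemia headings are objective and could be met by any patient on CRRT. The headings, however, restrict each event to one anticoagulant. Critically ill patients can bleed without heparin and can become hypocalcemic without citrate. To learn whether an agent adds to that background, the background must be counted in the same way in every group.

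Under the present wording it is counted in one group only. A table of the defined bleeding event by anticoagulant would show zero outside heparin whatever happened to those patients, and likewise for hypocalcemia outside citrate. Anticoagulation and patient safety are both named areas of interest, and the Background section says that natural variation will let outcomes be compared between practice patterns. A bleeding or hypocalcemia comparison by agent is therefore a natural use of the registry, and these two endpoints would mislead in it.

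**Working it through.** The documents give no event rates, no split by anticoagulant and no figure to reproduce. The check is therefore on the definitions, followed by an illustration on assumed values.

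**Step 1: who can have each defined event, by Table 3 category.**

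| Event as worded | Heparin | Citrate | None | Other |
|---|---|---|---|---|
| Major bleeding | possible | zero by definition | zero by definition | zero by definition |
| Symptomatic hypocalcemia | zero by definition | possible | zero by definition | zero by definition |
| Heparin-induced thrombocytopenia | possible | not applicable | not applicable | not applicable |

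The third row is no flaw, since that condition is specific to heparin by nature. The first two rows are zero because of the wording, not the biology.

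**Step 2: where a comparator event could still go.** A bleed on citrate that meets the hemoglobin and transfusion criteria can be recorded as a serious adverse event if it is judged related to CRRT. It then has no stated operational definition in the article. It also passes the same site review ("principal investigator to confirm appropriateness for inclusion").

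**Step 3: size of the artefact.** Let r be the true rate of criteria-meeting bleeds, equal in all groups, and let a (between 0 and 1) be the share of heparin bleeds judged heparin-related and kept after review.

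- Counted rate on heparin = a × r.
- Counted rate in every other group = 0.
- Apparent difference = a × r, which is at most r. The true difference is r − r = 0.

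Upper bound (a = 1), for assumed r of 1%, 2%, 5% and 10%: spurious differences of 1, 2, 5 and 10 percentage points.

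Counts at the target of 2000 patients, with assumed r = 5% and a = 1:

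| Assumed heparin share | Heparin patients | Heparin bleeds counted | Other patients | Other bleeds not counted |
|---|---|---|---|---|
| 10% | 200 | 200 × 0.05 = 10 | 1800 | 1800 × 0.05 = 90 |
| 25% | 500 | 500 × 0.05 = 25 | 1500 | 1500 × 0.05 = 75 |
| 50% | 1000 | 1000 × 0.05 = 50 | 1000 | 1000 × 0.05 = 50 |

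If only half of the heparin bleeds were attributed to heparin (a = 0.5, assumed), the apparent difference at r = 5% would be 0.5 × 5 = 2.5 points instead of 5. The comparators would still show zero. The same algebra applies to hypocalcemia with citrate in the place of heparin.

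**Step 4: can the criteria be applied to everyone from the listed data?** Table 2 collects hemoglobin, platelets, ionized calcium and vasopressors daily in all patients, with laboratory values as available. Red-cell units are not a named field; fluid intake is recorded by type and volume, without naming blood products. Arrhythmia is not a named field in Table 2 or Table 3. Reconstruction is therefore largely possible but incomplete, and daily values may miss short-lived events.

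**The case against.** A reader might infer that safety cannot be compared across anticoagulation strategies at all. The documents do not support that. All CRRT-related serious adverse events are to be recorded, the three complications are only a focus within them, and most components of the two definitions are collected daily in every patient.

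Nor is a bleeding or hypocalcemia contrast between agents expressly planned. The between-agent hypotheses in the Discussion concern circuit life and workload. The other anticoagulation comparison is between citrate protocols, for which the citrate definition of hypocalcemia is suitable. The outcomes that Statistical analysis names for association testing are mortality, length of stay and duration of AKI, while further analyses are left to specific research questions.

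It can also be said that attributed complications are a legitimate registry construct: no heparin-attributed bleeds without heparin is then the correct count. Finally, the full difference r against zero requires that every heparin bleed be attributed to heparin, whereas the text calls for a judgement of relatedness. Report forms common to all sites, which are not shown, may contain more structure than the article does.

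All of this narrows the point, but does not remove it. Events counted by fixed criteria in one group and by discretion in another are not comparably ascertained. A relatedness call lowers the heparin count without restoring any comparator event. The wording is also adopted as an outcome in a study that names anticoagulation and patient safety as areas of interest.

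**Conclusion.** The point holds for two endpoints: major bleeding and symptomatic hypocalcemia, as worded, cannot be compared between anticoagulation strategies. With equal true rates, the spurious difference in the defined bleeding event runs up to the full heparin rate. The 1 to 10 point range rests on assumed rates of 1% to 10% and on every heparin bleed being attributed to heparin, so it is an upper bound and not an estimate. The structural zero takes the anticoagulant in the event headings to be the CRRT anticoagulant recorded in Table 3.

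The primary outcome, survival at ICU discharge, is unaffected, as are comparisons of hypocalcemia between citrate protocols and the heparin-induced thrombocytopenia definition. Differences between centres in the site review are possible, but the documents do not show them. The change should be made because it is cheap and removes differential ascertainment from a named outcome.

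**What to change.** Take the anticoagulant out of the two event headings. Apply the existing hemoglobin and transfusion criteria, and the existing ionized calcium criteria with hypotension or arrhythmia, to all patients whatever the anticoagulant, with thresholds unchanged. Tabulate events by the anticoagulant in use at the time. Record attribution to heparin or citrate, and the outcome of the site investigator's review, as separate fields that do not remove events. Leave heparin-induced thrombocytopenia heparin-specific.

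The cost is revised form wording, explicit fields for red-cell units and arrhythmia, and more events counted and reviewed in the other groups. Common definitions remove the ascertainment artefact only. Agents are not randomised, so any between-agent comparison would still need adjustment for confounding.

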### Statistical analysis

All descriptive data will be analyzed using standard statistical methods. CRRTnet will assess for potential associations between patient characteristics, CRRT initiation and prescription parameters, and patient outcomes (mortality, length of stay, duration of AKI) using ANOVA (for normally distributed variables) or Kruskal-Wallis (for non-normally distributed variables). Multivariate proportional hazards models will be constructed, with initial inclusion of variables with <0.2 significance in univariate analyses. Additional analyses of registry data will be developed based on specific research questions.

Data analyses will be performed by Technomics Research, LLC (Minneapolis, MN) and guided by the CRRTnet registry board.

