One novel aspect of CRRTnet is the capture and analysis of machine data. These data record all machine measurements to the second, and include pressure measurements (e.g. access and return line pressures, filter pressures, transmembrane pressures), alarms and response to alarms, any changes in prescription (including blood, dialysate and replacement flow rates), interruptions, and actual delivered therapy. To our knowledge, this is a relatively untapped source of information, and one goal of CRRTnet will be to develop algorithms for processing the information downloaded from the CRRT machine memory cards. One of the challenges of CRRT is the complexity of therapy and the increased associated workload compared to intermittent therapies [31]. By utilizing the detailed treatment data, we will be able to characterize alarm frequency and provide more precise estimates on interface time required to maintain this therapy. This information may be helpful to administrators in determining nursing models and CRRT educational programs. In addition, nursing workload can be considered an important secondary outcome that may vary between and within centers depending on variations in CRRT protocol. For example, we hypothesize that regional citrate anticoagulation will be associated with less workload compared to non-citrate anticoagulation. It will also be interesting to compare associated workload between different citrate protocols, especially if circuit filter life is similar.

An important strength of our study is that we are examining everyday practices. While findings from controlled clinical trials can sometimes be difficult to duplicate in the “real world” setting, we will provide a relatively unfiltered look. This may be particularly important when examining adverse events and complications of therapy. Conversely, it is important to recognize that CRRT is performed at a relatively high frequency at each of the study sites, which facilitates development of local expertise and maintenance of competency. Whether or not similar practices will result in similar outcomes at smaller centers with lower volumes is uncertain. Nonetheless, we believe that CRRTnet will provide important outcomes benchmarks for centers performing CRRT.

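### Inclusion of serious adverse events rests on review with the treating site's own investigator, so safety comparisons between centres or citrate protocols are open to differential ascertainment

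*Protocol article*

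**What the plan says.** The protocol article, under Operational definitions, starts with full capture: "All serious adverse events related to CRRT will be recorded, with a specific focus on the following complications". It then defines major bleeding on heparin, heparin-induced thrombocytopenia and hypocalcaemia on citrate. The criteria are largely objective; the bleeding definition, for example, begins with "Drop in hemoglobin of ≥1.0 g/dL within a 24 h period" and also requires transfusion. The section ends with the inclusion step: "All serious adverse events will be reviewed with each site’s principal investigator to confirm appropriateness for inclusion".

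Other sections bear on this step:

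- Primary and secondary outcomes lists CRRT-related adverse events among the additional outcomes and points back to these definitions. The primary outcome is survival at ICU discharge.
- Study oversight and consent describes the registry board as "comprised of the site principal investigators for each of the recruitment centers". Statistical analysis says the analyses are "guided by the CRRTnet registry board".
- Background gives a long-term aim to "establish benchmarks for best CRRT practice for centers both within and outside the study".
- Discussion plans to compare outcomes between citrate protocols, using the fact that these differ among the centres.
- Discussion also presents a fairly unfiltered view of everyday practice as a strength, adding: "This may be particularly important when examining adverse events and complications of therapy".

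**The concern.** The stated capture rule is that all CRRT-related serious events are recorded. The final sentence puts a second condition on top of it, with no stated test. The one person named at that step belongs to the centre where the event happened and can be expected to know which anticoagulant and protocol the patient received. Serious events outside the three defined complications have no written criteria at all, so for them judgement is the only gate.

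If sites differ in how readily they confirm events, recorded rates will differ even where care does not. Because citrate protocol is tied to centre, a site's confirmation habit moves together with the exposure being compared, and adjusting for patient characteristics cannot separate the two. If unconfirmed events are not kept, the share lost at each site cannot be measured afterwards.

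**Working it through.** **Text check.** Four statements, set side by side:

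1. All CRRT-related serious events are recorded, and three complications have written criteria (Operational definitions).
2. Inclusion then depends on a review with the site's principal investigator (same section).
3. The only oversight body named is made up of those investigators, and it also guides the analysis (Study oversight and consent; Statistical analysis).
4. These events are an outcome, and outcomes are compared across protocols that differ by centre (Primary and secondary outcomes; Discussion).

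Following 2 as written allows an event that satisfies 1 to be left out on grounds that may vary by site. Nothing in 3 checks this independently, and 4 is where it would show.

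**Illustration of size.** The document gives no adverse event rate and no confirmation rate, so there is no figure of the plan's to reproduce. Everything below rests on assumptions.

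- Patients per centre: 2000 / 4 = 500. The total of 2000 is the target under Sample size; the even split is assumed.
- True event rate p: equal in both centres, 2% to 15% (assumed).
- Shares confirmed c1 and c2: assumed.
- Observed rates: p1 = p × c1 and p2 = p × c2. The observed risk ratio is c2 / c1, whatever the value of p.

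One worked case, p = 10%, c1 = 90%, c2 = 60%:

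- Events: 500 × 0.10 × 0.90 = 45 and 500 × 0.10 × 0.60 = 30, or 9% v 6%.
- Risk ratio: 0.06 / 0.09 = 0.67.
- z = 0.03 / √(0.09 × 0.91/500 + 0.06 × 0.94/500) = 0.03 / 0.0166 = 1.80.

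A milder case, p = 10%, c1 = 100%, c2 = 80%: 10% v 8%, with z = 0.02 / √(0.10 × 0.90/500 + 0.08 × 0.92/500) = 1.11.

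The chance of a nominally significant false difference (two-sided 0.05, counting only the direction that the filtering produces) is Φ((|p1 − p2| − 1.96 × SE0) / SE1). SE0 uses the pooled rate and SE1 the separate rates, with 500 per centre:

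| Confirmed, centre 1 v centre 2 | Risk ratio | p = 2% | p = 5% | p = 10% | p = 15% |
|---|---|---|---|---|---|
| 100% v 90% | 0.90 | 4% | 6% | 8% | 10% |
| 100% v 80% | 0.80 | 7% | 12% | 20% | 28% |
| 100% v 70% | 0.70 | 11% | 22% | 40% | 57% |
| 90% v 60% | 0.67 | 12% | 24% | 44% | 62% |

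With no filtering, the chance in one direction would be 2.5%. Small differences in confirmation therefore matter little and large ones matter a good deal. The defined complications arise only in patients given heparin or citrate, so the true denominators may be below 500 per centre. That lowers these chances but leaves the bias in the risk ratio unchanged.

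**What could be recovered.** Table 2 collects haemoglobin, platelets, ionized calcium, vasopressor drug and rate, and type and volume of fluid intake. Table 3 collects the type of anticoagulation. Candidate bleeding events, and hypocalcaemia events with rising pressor need, could largely be rebuilt from these. Arrhythmia and the serotonin release assay appear in none of Tables 1 to 3. Relatedness, and serious events outside the three definitions, could not be rebuilt either.

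**The case against.** The strongest reply is that the sentence is an ordinary quality check. It follows directly on the definitions, so appropriateness may simply mean that an event meets them. Events are reviewed with the investigator, which is not the same as the investigator deciding alone. Inclusion may refer to an analysis and not to the registry. This is also a condensed article, and retention of unconfirmed events and adjudication forms may be set out in a fuller document.

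Much of this stands, and it limits what can be claimed. A reader might infer that each investigator alone decides which events count, or that criteria-meeting events are deleted. The text says neither. A reader might also infer that centre-specific safety rates will be benchmarked. No section says so: benchmarking is mentioned in general terms, and the planned comparison by citrate protocol concerns outcomes broadly. Nor does the remark about an unfiltered view amount to a contradiction. It contrasts everyday practice with controlled trials and is only in tension with a local confirmation step. Finally, the confirmation shares above are assumed, and even the 90% v 60% case at a 10% rate gives z = 1.80, short of 1.96.

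What survives is the stated rule itself. It makes inclusion rest on a review in which only the local investigator is named, against a standard that is not given, for an outcome that the registry means to study across centre-linked practices. That does not depend on anything the article left out.

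**Conclusion.** The point holds as a cheap improvement. Following the rule as written permits centre-dependent ascertainment of CRRT-related serious adverse events, and no independent check is described. Comparisons of these events between centres, or between citrate protocols that differ by centre, are therefore open to bias.

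The direction and size cannot be known from the document. Under the assumptions shown, the false risk ratio equals the ratio of the confirmation shares, for example 0.70 for 100% v 70%. The chance of a false significant difference then ranges from about 11% at a true rate of 2% to 57% at 15%; for 100% v 90% it is only about 4% to 10%. Survival at ICU discharge is unaffected. The daily data would allow part of any loss of bleeding and hypocalcaemia events to be detected.

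**What to change.** Replace the final sentence of Operational definitions with a rule on these lines:

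- Every event that meets the written objective criteria (laboratory, transfusion, pressor or arrhythmia, as defined) in a patient receiving the named anticoagulant is entered and kept. So is every other serious event reported as possibly CRRT-related.
- The site investigator's judgement of relatedness or appropriateness is recorded in a separate field and cannot remove an event.
- Safety rates are reported first on all criteria-meeting events and second on those confirmed as related, with the share not confirmed shown for each site.
- Bleeding and hypocalcaemia events are cross-checked against the daily laboratory, pressor and intake data already collected. Because recruitment is active, this check also helps with patients already enrolled.

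Masked review by an investigator from another centre is not recommended. Attribution to heparin or citrate cannot be judged by someone masked to the anticoagulation, and such review would need chart work beyond the de-identified registry data.

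The cost is one extra form field and some programming for the cross-check. Reported event rates will be somewhat higher and less specific, because events that a site would not have confirmed now count in the first analysis; the second analysis shows how much this matters.
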